## Abstract

This study will investigate the effects of high-frequency Transcranial Magnetic Stimulation (TMS) on lower limb muscle strength, using an isokinetic dynamometer to measure strength changes. The research will involve 50 healthy sedentary male participants aged 18–25, randomized into active and sham groups. The protocol will integrate TMS with surface electromyography (sEMG) to assess muscle activation and enhance accuracy. The aim will be to explore whether TMS can influence peripheral neuromuscular characteristics, improving muscle performance.

The protocol will involve a double-blind, randomized design and the use of an isokinetic dynamometer for precise muscle strength measurement. By employing TMS, which enhances cortical excitability, and evaluating muscle performance via controlled assessments, the study will seek to provide reliable pre- and post-intervention data. The study’s sample calculation will ensure adequate statistical power and account for potential attrition, with 50 participants included.

This research will have potential clinical applications, particularly for muscle rehabilitation and performance optimization. However, it will face limitations, such as a male-only sample and variability in individual responses to TMS. Despite these challenges, the study's findings could inform future therapeutic strategies for enhancing muscle strength and contribute to advancing TMS applications in both clinical and athletic settings.

Specifications table

**Table utbl0001:** 

Subject area:	Neuroscience
More specific subject area:	Noninvasive Neuromodulation
Name of your protocol:	TMS on force lower limb muscles of healthy individuals
Reagents/tools:	TMS MagPro R30 Biodex System Pro isokinetic dynamometer New Miotool
Experimental design:	Randomized clinical trial with sedentary individuals, comparing placebo and EMT intervention, assessing muscle strength before and after stimulation.
Trial registration:	Informed consent was obtained from the participants.
Ethics:	Informed consent was obtained from all patients after patient eligibility was confirmed. The entire research project was submitted to the Research Ethics Committee of the Federal University of Espírito Santo, and approval was obtained in accordance with substantiated opinion number CAAE80859824200005060.
Value of the Protocol:	The protocol aims to evaluate the potential of improving muscle strength through transcranial magnetic stimulation

## Background

Skeletal muscles exhibit four primary performance characteristics: (1) maximum force production, (2) contraction velocity, (3) maximum power generation, and (4) contraction efficiency. Maximum force production is dictated by the amount of myosin and actin, as force is generated through cross-bridges formed by myosin binding to actin, which directly correlates with the muscle fiber cross-sectional area.

Contraction velocity refers to the maximum speed at which a muscle fiber can shorten, a property dependent on the velocity of the cross-bridge cycle. Maximum power generation is defined as the product of force production and shortening velocity (force × velocity). Lastly, contraction efficiency quantifies the energy expenditure relative to the force generated, calculated as the ratio of energy consumed to force output [1].

Each motor neuron originating from the spinal cord innervates multiple muscle fibers, with the number of fibers varying according to muscle type. All muscle fibers innervated by a single nerve fiber constitute a motor unit. When the central nervous system (CNS) sends a weak signal for muscle contraction, smaller motor units are preferentially recruited over larger ones. As CNS signal strength increases, larger motor units are activated, with some capable of producing up to 50 times the contractile force of smaller units. This recruitment pattern, known as the size principle, allows fine gradation of force during weak contractions while ensuring progressive force generation when needed [2].

At low stimulation frequencies, skeletal muscle contractions occur sequentially. As frequency increases, contractions begin before the previous ones have fully relaxed, summating to enhance total contractile force. Beyond a critical frequency, contractions fuse into a smooth, continuous contraction. At slightly higher frequencies, maximal force production is reached, beyond which further increases in frequency no longer enhance contractile force [2].

Transcranial magnetic stimulation (TMS) is a non-invasive brain stimulation technique [3]. High-frequency TMS (>5 Hz) has been shown to enhance cortical excitability, particularly within the motor cortex [4].

Muscle strength can be assessed using various methods, including maximum weight lifted with exercise equipment, maximum isometric torque, and maximum isokinetic torque at specific or nonspecific angles. The isokinetic dynamometer enables precise evaluation of maximum concentric and eccentric muscle strength at constant velocities over a controlled range of motion [5].

Since TMS, when applied to the CNS, has the potential to influence the characteristics of the peripheral neuromuscular system, this study aims to investigate whether TMS can enhance muscle performance. The isokinetic dynamometer is used as a reference tool to ensure reliable pre- and post-intervention measurements, facilitating reproducibility in future studies and clinical applications.

## Description of protocol

This study aims to evaluate the effects of electromagnetic stimulation on lower limb muscle strength, using an isokinetic dynamometer for assessment. Surface electromyography (sEMG) is employed to determine the intensity of TMS by capturing muscle activation at baseline, thereby enhancing the protocol's accuracy.

This is a double-blind, randomized clinical trial conducted at the School Clinic of the Federal University of Espírito Santo (UFES). The study includes 50 healthy participants, aged 18 to 25, classified as sedentary according to the International Physical Activity Questionnaire (IPAQ) and meeting the inclusion criteria (Fig. 1).

**Fig. 1 fig0001:**
[figure not shown]
Study flowchart.

## Sample calculation

To date, no studies have assessed the effects of TMS on large muscle groups, such as the quadriceps, using an isokinetic approach. Additionally, no established clinically significant difference exists for isokinetic quadriceps strength.

For this study, the effect size (Cohen’s f) for the statistical calculation of a two-way (between-within) ANOVA with two groups and two time points was set at 0.20. The following parameters were applied: effect size = 0.20, alpha = 0.05, statistical power = 80 %, number of groups = 2, number of measurements = 2, correlation between repeated measures = 0.5, and non-sphericity correction = 1. Based on these parameters, 42 volunteers were required. Considering a potential 20 % sample attrition, the final sample size was adjusted to 50 participants, with 25 allocated to the sham group and 25 to the intervention group (Table 1).

**Table 1 tbl0001:** Inclusion and exclusion criteria study.

Inclusion criteria	Exclusion criteria
1. Men aged between 18 and 50 years.	1. Have had deep brain stimulation (DBS) surgery.
2. Identified as sedentary or minimally active according to the IPAQ questionnaire.	2. Presence of associated neurological diseases.
3. Physically capable of performing isokinetic dynamometer tests.	3. Orthopedic conditions that limit participation in study.
4. Be able to understand instructions for the isokinetic dynamometer tests.	4. History of seizures or traumatic brain injury.
5. Scoring adequately on the Mini-Mental State Examination, adjusted for educational level (26 for higher education, 18 for primary and secondary education, 13 for illiterates).	5. Acute strain (musculotendinous unit) or sprain (non-contractile tissue).
6. Able to give informed consent in accordance with institutional policies.	6. Soft tissue healing restrictions (e.g., post-surgery).
7. Capable of completing all physical and cognitive test requirements as defined.	7. Pain during protocol execution.
	8. Extremely limited range of motion (ROM).
	9. Severe effusion.
	10 Joint instability.
	11. Subacute or chronic third-degree sprains.
	12. Significant knee ROM limitation.
	13. Lower limb joint laxity.

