In the active group, TMS will be delivered using a Cool B70 butterfly coil (Magventure, Denmark) positioned over the primary motor cortex. Stimulation intensity will be set at 100 % of the motor threshold, defined as the lowest intensity capable of inducing peripheral muscle contraction, verified via EMG. The stimulation protocol will follow the 10/20 EEG system, with Cz serving as the common stimulation site for all participants. Coil orientation will depend on the dominant limb: for right-leg-dominant participants, the coil will be tilted 45° to the left, while for left-leg-dominant participants, it will be tilted 45° to the right. The protocol will consist of 30 trains of 100 pulses at 20 Hz, with each train lasting 5 s and separated by a 20-second inter-train interval, totaling 3000 pulses over approximately 20 min. This procedure will be repeated for five consecutive days, with individual motor threshold reassessed daily to ensure accurate stimulation parameters.

The placebo group will receive sham stimulation using a Cool B70 butterfly coil (Magventure, Denmark) designed to replicate the sound and timing of active stimulation without delivering a magnetic current.

On the fifth day, following stimulation, both groups will rest for five minutes before performing the same isokinetic dynamometer test as on the first day. The collected data will be compared with pre-stimulation results.

The study will be conducted at the School Clinic of the Federal University of Espírito Santo (UFES). All team members will receive standardized training on the use of the isokinetic dynamometer and TMS equipment. The TMS operators will remain blinded to group allocation, as the stimulator will be pre-configured by an external researcher with no direct contact with participants or investigators. During both isokinetic tests, participants will be instructed to exert maximum effort throughout all repetitions, with auditory stimuli provided to maintain engagement during testing.

Participants unable to complete the test will be classified as "incomplete tests," and a replacement participant will be recruited.

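### The named pre/post ANOVA is valid but wastes the baseline; ANCOVA on day-5 strength tests the same between-arm effect with 25% less variance at the plan's correlation of 0.5

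*Protocol article*

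**What the plan says.** The only statistical test in the protocol article appears under Sample calculation, as the basis for sizing the trial: a "two-way (between-within) ANOVA with two groups and two time points". Its inputs are "effect size = 0.20, alpha = 0.05", "statistical power = 80" per cent, "number of groups = 2, number of measurements = 2", "correlation between repeated measures = 0.5" and "non-sphericity correction = 1". From these the article concludes that "42 volunteers were required", and it raises the number to 50 (25 per arm) for 20% attrition.

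Materials and methods says that random assignment follows the baseline measurements and that outcome assessors are blinded. Strength is tested before stimulation on day 1 and again after stimulation on day 5. Of the day-5 data it says: "The collected data will be compared with pre-stimulation results". Baseline is not mentioned as a covariate. The experimental-design row of the Specifications table describes a comparison of placebo with the intervention, with strength assessed before and after stimulation.

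**The concern.** With two groups and two times, the group-by-time interaction compares mean change between arms. A change score subtracts the whole baseline value, which is the best weight only if baseline predicts the follow-up value one-for-one. At a correlation of 0.5 that subtracts too much: the noise brought in by the baseline cancels the benefit of removing differences between participants. ANCOVA estimates the weight from the data. In a randomised trial with a pre-randomisation baseline, it targets the same between-arm difference.

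The trial therefore collects a baseline on everyone and, under the named test and its own planning correlation, gains no precision from it. With at most 50 participants, that can decide whether a real effect is detected.

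A smaller matter is that the sentence on comparing day-5 data with pre-stimulation results does not say whether the contrast is between arms or within an arm. Only a between-arm contrast separates stimulation from retest gains that the sham arm may share.

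**Working it through.** **Inputs from Sample calculation:** f = 0.20, alpha 0.05 (taken as the usual non-directional F test), power 80%, 2 groups, m = 2 measurements, rho = 0.5, non-sphericity correction 1, 1:1 allocation. If 20% are lost, 50 × 0.8 = 40 are analysed.

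**Assumption:** f is the interaction effect size. In a 2×2 layout each cell then deviates by f outcome SDs, so the between-arm difference in change is 4f = 0.8 outcome SD. The article does not state this conversion.

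**Step 1: the plan's own figure.** The interaction noncentrality is f²·N·m/(1−rho) = 0.04 × 2N/0.5 = 0.16N, with 1 and N−2 df. The smallest even N giving 80% power is 52, so the stated 42 is not reproduced. At 42 the power is 71.6%. Within this formula, 42 appears only with an unstated change of input: a one-sided 0.05 test, rho = 0.6, or f of about 0.225.

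**Step 2: variances, in units of the outcome variance.**
- Day-5 value alone: 1.
- Change score: 2(1−rho) = 2 × 0.5 = 1.
- ANCOVA: 1−rho² = 1−0.25 = 0.75.

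At rho = 0.5 the change score is exactly as noisy as the day-5 value alone. The ratio of ANCOVA to change-score variance is (1−rho²)/[2(1−rho)] = (1+rho)/2. This is 0.75 at rho 0.5, 0.80 at 0.6 and 0.90 at 0.8, giving savings of 25%, 20% and 10%.

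**Step 3: power for the same 0.8 SD difference, rho = 0.5.** The ANCOVA noncentrality is 0.8²·N/(4 × 0.75) = 0.2133N, with 1 and N−3 df.

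| Analysed | Interaction: noncentrality | Interaction: power | ANCOVA: noncentrality | ANCOVA: power |
|---|---|---|---|---|
| 40 | 6.40 | 69.3% | 8.53 | 81.2% |
| 42 | 6.72 | 71.6% | 8.96 | 83.1% |
| 50 | 8.00 | 79.1% | 10.67 | 89.2% |

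The smallest even N for 80% power is 52 for the interaction and 40 for ANCOVA. A simulation of 20,000 trials per N gave 69.6%, 71.3% and 79.1% for the change test, and 80.5%, 82.0% and 88.4% for ANCOVA.

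**Step 4: dependence on rho.** There are two ways to hold the effect fixed.
- *Effect fixed at 0.8 outcome SD, 42 analysed.* Interaction versus ANCOVA power is 80.7% versus 88.5% at rho 0.6, 90.4% versus 94.3% at 0.7, and 97.9% versus 98.8% at 0.8.
- *Effect fixed at 0.8 SD of the change.* The interaction noncentrality stays at 0.16N, so its power stays at 69.3% (40 analysed) and 71.6% (42). ANCOVA power at 40 and 42 is 78.7% and 80.7% at rho 0.6, 76.2% and 78.3% at 0.7, and 73.8% and 76.0% at 0.8.

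ANCOVA has the higher power in every case, but its margin shrinks as rho rises.

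**The case against.** The strongest reply is that nothing here is an error. The interaction test is valid, it removes any practice gain common to both arms, and it is named only to size the trial. A condensed article may leave covariate adjustment, and the choice of the ANOVA term that carries the conclusion, to an analysis plan that is not shown and may already specify ANCOVA. This largely stands. Not naming the decisive term is no fault here. What remains is that the one test the article does name is less efficient than an alternative that needs no new data.

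The size of the gain is also open to challenge. It rests on rho = 0.5, for which the article cites no source, and on the 0.8 SD reading of f. Incomplete tests are to be replaced, so 50 may be analysed, and the interaction then already has 79%. These limits are accepted.

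Three stronger readings are tempting, and the documents do not support them:
- *That the trial plans only a before-after comparison.* The Specifications table sets placebo against the intervention, the sizing uses two groups, and the sentence on pre-stimulation results directly follows one about both groups. It is ambiguous, but it commits to no within-arm test.
- *That practice gains will produce false positives.* This needs a within-arm test that is not planned and a practice gain that the article does not give. Practice tests also precede the day-1 assessment.
- *That ANCOVA repairs the sample size.* It does not make 42 the right answer for the ANOVA named; the stated inputs give 52.

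**Conclusion.** The point holds as a matter of efficiency. At the article's own correlation, the interaction test gains no precision from a baseline measured before randomisation, while ANCOVA cuts the variance of the between-arm effect by 25%. In power this is worth 10 to 12 percentage points: 69% to 81% with 40 analysed, 72% to 83% with 42, and 79% to 89% with 50. These figures assume rho = 0.5, f = 0.20 read as an interaction of 0.8 outcome SD, and a two-sided 0.05 test. It would be fair to say that ANCOVA brings power up to about 80% only for 40 to 42 analysed under those assumptions; with 50 it adds to a test already near 80%. The change is worth making because it uses data already collected and the variance advantage holds at any correlation below 1, at the price of one degree of freedom.

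**What to change.** - Name as primary analysis an ANCOVA of the day-5 post-stimulation strength outcome on arm, with the day-1 pre-stimulation value of the same measure (same test and speed) as covariate. A mixed model constraining the arms to a common baseline mean is an equivalent choice.
- Report the adjusted active-minus-sham difference with its 95% CI.
- Reword the sentence on pre-stimulation results to say that the comparison is between arms, and that within-arm pre-post results are descriptive only.
- Recalculate the required number for the test actually used, stating the effect size convention and the correlation. With the article's inputs this is 40 for ANCOVA and 52 for the interaction. Allowing for 20% attrition, that means enrolling 40/0.8 = 50 or 52/0.8 = 65.

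The cost is wording and one recalculation, with no extra visits or measurements. The investigators must also fix which strength measure is primary, because tests are run at 30, 60 and 180°/s; that choice is theirs. If the full analysis plan already specifies ANCOVA, only the sample-size basis and the ambiguous sentence need attention.

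### The stated inputs require 52 participants, not 42; with 42 analysed the power is about 72%, not 80%

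*Protocol article*

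**What the plan says.** The Sample calculation section of the protocol article bases the sample size on a "two-way (between-within) ANOVA with two groups and two time points was set at 0.20", that figure being Cohen's f. It then lists "effect size = 0.20, alpha = 0.05", power of 80%, "number of groups = 2", "number of measurements = 2, correlation between repeated measures = 0.5", and a non-sphericity correction of 1. From these it concludes: "Based on these parameters, 42 volunteers were required". It allows for 20% attrition and sets the final size at 50, with 25 per group.

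The Abstract relies on the result, saying that the "sample calculation will ensure adequate statistical power and account for potential attrition, with 50 participants included".

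The same section says that no earlier study has used isokinetic testing of TMS effects on large muscle groups and that no clinically significant difference is established for quadriceps strength. The calculation is thus the only justification the article gives for the sample size.

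**The concern.** Every input needed for the power calculation is given, so the stated sample size can be checked directly, and 42 is lower than those inputs produce. Either the required number is wrong or one of the listed inputs is not the one used. On either reading the paragraph misreports the calculation.

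What is at stake is how the result will be read. If the trial finds no difference, readers will take it that an effect of the stated size had an 80% chance of being detected. On the plan's own inputs the chance is lower, and the allowance for attrition does not exist, because 50 is already below the number needed before any loss. The effect is also larger than f = 0.20 may suggest to a reader: under the convention used here it is a difference in change of 0.8 SD.

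**Working it through.** **Inputs, all from the Sample calculation section.** f = 0.20; alpha = 0.05; target power 80%; groups k = 2; measurements m = 2; correlation ρ = 0.5; non-sphericity correction ε = 1; 1:1 allocation. No sidedness is given. An ANOVA F test is non-directional, and with one numerator degree of freedom it equals a two-sided t test.

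**Test.** The group-by-time interaction is the term that compares change between active and sham.

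**Formula.** Noncentral F with

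- λ = f² × N × m × ε / (1 − ρ) = 0.04 × N × 2 × 1 / 0.5 = 0.16N
- df₁ = (k − 1)(m − 1) = 1
- df₂ = (N − k)(m − 1) = N − 2

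**Attempt to reproduce 42.**

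| N analysed | λ | Power |
|---|---|---|
| 40 | 6.40 | 69.3% |
| 42 | 6.72 | 71.6% |
| 50 | 8.00 | 79.1% |
| 51 | 8.16 | 79.96% |
| 52 | 8.32 | 80.7% |

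The stated 42 is not reproduced. The smallest N with at least 80% power is 52, or 26 per group.

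**Check by change scores.** In a 2×2 layout, f = 0.20 means interaction effects of ±0.2 SD in the four cells, so the active–sham difference in change is 4 × 0.2 = 0.8 SD. The SD of a change score is √[2(1 − 0.5)] = 1 SD. The interaction test is then a two-sample t test with a standardised difference of 0.8. With 21 per group its squared noncentrality is 0.8² × 21/2 = 6.72, the same λ as above. A simulation of 200,000 trials with 21 per group gave 71.7% power.

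**Other tests and conventions at the same inputs.**

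- Within-participant main effect: N = 52.
- Between-group main effect, λ = f²Nm/[1 + (m − 1)ρ]: N = 150.
- Two other definitions of f, with λ = f²N(m − 1) or f²(N − k)(m − 1): N = 200 or 202.
- Normal approximation on change scores: N = 50, with 73.6% power at 42.

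**What would give 42.** Each of these changes something the text states, or adds something it does not:

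- correlation 0.6: 80.7% at 42
- three measurements at correlation 0.5: 80.3% at 42
- f of about 0.22: 80% at 42, a difference in change of about 4 × 0.22 = 0.89 SD before rounding f
- a one-sided 0.05 test: 81.7% at 42

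**Attrition.** Losing 20% of 50 leaves 40, with 69.3% power. To end with 52 after 20% loss needs 52/0.8 = 65, or 66 if balanced. Even from the stated 42, 42/0.8 = 52.5, so 53 would be needed; going from 50 to 42 allows for 16% loss.

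**The case against.** The strongest reply is that the trial enrols 50, not 42. With all 50 analysed the power is 79.1%, within a point of the target. The Materials and methods section also says that participants who cannot complete the test will be replaced, which could keep the number of complete cases near 50. This stands as a limit on the practical shortfall. It does not rescue the calculation: the Sample calculation section itself budgets 20% attrition, and 50 is below the 52 needed before any loss.

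A second reply is that the final analysis may not be this ANOVA. The article names it for the sample size and otherwise says only that results will be compared with those before stimulation. A baseline-adjusted analysis (ANCOVA) at the same correlation would have about 83% power with 42 analysed and about 81% with 40. This too is fair, but it is not the calculation reported, so it cannot justify the reported figure.

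Third, several different changes lead to 42, so the source of the error cannot be identified from the article. That is right, and it is a reason not to guess. Three measurements, for instance, would contradict the two time points stated in the same paragraph.

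Finally, the Abstract gives no power figure of its own. Its sentence is a consequence of the error, not a second error.

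**Conclusion.** The stated sample size is wrong as written. On the listed inputs, 80% power requires 52 analysed participants; 42 gives 71.6%. The planned 50 give 79.1% with full retention and 69.3% with the 20% loss the plan allows for. The shortfall is therefore under one percentage point if everyone is retained or fully replaced, and about eleven points at the planned attrition.

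This rests on the group-by-time interaction as the test of interest, a non-directional F test at 0.05, and the convention for f under which the correlation enters λ as shown. The other conventions for f that were tried, and the between-group main effect, require far more participants, so they do not favour 42. The conclusion needs no figure from outside the article.

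**What to change.** Rerun the calculation and correct the Sample calculation paragraph so that inputs, required number and power agree.

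- **If enrolment stays at 50:** give 52 as the number the listed inputs require for 80% power. State that 50 gives about 79% with no loss and about 69% with 20% loss, and say how the replacement of incomplete tests affects the number analysed.
- **If 80% power after 20% loss is wanted under this ANOVA:** plan for 65, or 66 if balanced.
- **If the source calculation used an input other than the one printed:** report that input and justify it on its own merits. A value should not be chosen afterwards because it returns 42.

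In each case, state the detectable effect as a difference in change (0.8 SD at f = 0.20 and correlation 0.5), and reword the Abstract sentence to match. As an option, the sponsor could base the power on a baseline-adjusted ANCOVA, which gives about 81% with 40 analysed at the same correlation, provided that this is also the analysis specified.

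The cost of the first option is one reworded paragraph and one Abstract sentence, with a less favourable power figure and no extra participants. The second option means 15 or 16 more participants than planned.

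### The 20% attrition allowance is misapplied: 50 enrolled keeps the stated 42 only up to 16% loss, and 20% loss leaves 40

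*Protocol article*

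**What the plan says.** The Sample calculation section sizes the trial for a two-way (between-within) ANOVA. Its inputs are "effect size = 0.20, alpha = 0.05, statistical power = 80" %, "number of groups = 2, number of measurements = 2" and "correlation between repeated measures = 0.5, and non-sphericity correction = 1". It then states: "Based on these parameters, 42 volunteers were required". The next step opens with "Considering a potential 20 % sample attrition" and ends: "the final sample size was adjusted to 50 participants, with 25 allocated to the sham group and 25 to the intervention group".

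The abstract presents the result as settled, saying that the calculation will secure adequate power and "account for potential attrition, with 50 participants included".

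One other sentence bears on losses. Materials and methods says that a participant who cannot complete the test is classed as an incomplete test "and a replacement participant will be recruited". The Sample calculation section does not mention this rule.

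**The concern.** An attrition allowance exists so that, after the expected losses, the number analysed is still the number required. Attrition is a share of those enrolled, so the required number must be divided by the proportion retained. Adding 20% of the required number always gives too few, because the losses are then taken from the larger enrolled total. The stated 50 looks like the result of that addition.

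At stake is whether the sample-size statement is true as written. Anyone relying on it, or replicating the trial, will conclude that 50 protects the requirement of 42 against 20% loss. On the document's own figures it does not.

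**Working it through.** **Inputs, all from the Sample calculation section.** Required number 42; attrition 20%; enrolled 50 as 25 + 25; Cohen's f = 0.20; alpha 0.05; 2 groups; 2 measurements; correlation 0.5; non-sphericity correction 1.

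**Step 1. Reproduce the plan's 50.** Adding 20% to the requirement: 42 × (1 + 0.20) = 50.4. Rounded down, this is 50, the stated figure. Rounded up, as is usual for a sample size, it would be 51, or 52 in equal arms.

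**Step 2. Apply the stated loss to the stated enrolment.** 50 × (1 − 0.20) = 40, or 20 per arm. The shortfall against the requirement is 42 − 40 = 2.

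**Step 3. Find the loss that 50 can absorb.** 1 − 42/50 = 8/50 = 16%.

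**Step 4. Find the enrolment that 20% loss would need.** 42/(1 − 0.20) = 52.5, so 53, or 54 (27 per arm) with equal arms. That is 3 to 4 more than planned.

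**Step 5. Cost in power on the stated inputs.** For the group-by-time interaction under the usual within-between convention, the noncentrality is λ = f² × N × m/(1 − ρ) = 0.04 × N × 2/0.5 = 0.16N, with 1 and N − 2 degrees of freedom, and the F test is at 0.05.

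| N analysed | λ | Power |
|---|---|---|
| 40 | 6.40 | 69.3% |
| 42 | 6.72 | 71.6% |
| 50 | 8.00 | 79.2% |
| 52 | 8.32 | 80.8% |

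The attrition step is the move from 42 to 40: 71.6% − 69.3% = 2.3 points on these rounded figures.

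**Step 6. Cost if 42 is taken at face value.** Suppose 42 does give 80% for whatever test the plan intended. With the same degrees of freedom, λ at 42 must then be about 8.24, or 0.196 per participant. At 40, λ is about 7.85 and power is 78.0%. The loss is again about 2 points.

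**Step 7. Separate the two sources.** The gap between 80% and 69.3% is 10.7 points. Of these, 80 − 71.6 = 8.4 arise because 42 does not reach 80% under the Step 5 convention, where 52 would be needed. Only 71.6 − 69.3 = 2.3 arise from attrition.

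**The case against.** Four points can be made for the plan.

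**Adding the percentage is a common shortcut, and the gap is trivial.** Two participants matter less than the uncertainty in an effect size of 0.20 that the section sets without prior isokinetic data. The 20% is itself described only as potential. All of this stands as to size. It does not make the statement correct: the 20% is described as attrition of the sample, and even the shortcut gives 50.4, which 50 does not reach.

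**Incomplete participants are replaced.** This is the strongest point. If losses are made good, the number analysed need not fall to 40. A reader might infer that the trial will end with 40; the document does not support that, because the replacement rule may offset some of the loss. But the rule names only participants unable to complete the test. The document does not say whether someone who leaves during the five days for another reason is replaced, or how replacement fits with a fixed 25 + 25. If every loss were replaced, the 20% allowance would have no purpose. The rule softens the consequence and leaves the arithmetic as it is.

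**The power figures depend on a convention that the document does not name.** This is true. Neither the ANOVA term nor the effect-size option is stated. For example, an F-test alpha of 0.10 (equivalent to one-sided 0.05) would reproduce 42, and power at 40 would then be 79.9%. Steps 1 to 4 need no such assumption.

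**The article condenses a fuller protocol.** Nothing is claimed to be missing here. The three figures are all printed, and they disagree.

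**Conclusion.** The point holds as an arithmetic error of modest size. With 50 enrolled, the stated 42 is kept only up to 16% loss; at the stated 20%, and without replacement, 40 remain. This rests only on figures printed in the Sample calculation section.

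The attrition step alone costs about 2 points of power: 71.6% to 69.3% on the stated inputs, assuming the usual within-between interaction test at two-sided 0.05, or 80% to about 78% if 42 is accepted as it stands.

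Two stronger readings should be resisted. A reader might infer that the misapplied allowance lowers power from 80% to 69%. It does not; most of that gap comes from the base figure of 42, which is a separate question and should not be counted twice. A reader might also infer that the trial must enrol 65 (52/0.8), or 66 in equal arms. Those figures start from 52 rather than the plan's 42, and so depend on a test and effect-size convention that the document does not name.

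**What to change.** Restate the final sentence of the Sample calculation section in one of two ways:

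- recruiting 50 tolerates 16% attrition while keeping 42; or
- with 20% attrition, 40 participants will be analysed.

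In either case, give the power recomputed for that number, naming the ANOVA term and effect-size convention used: about 72% at 42 or about 69% at 40 under the stated inputs. The first sentence without its power figure would leave the impression that 42 gives 80%. Change the matching claim in the abstract.

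In the same edit, reconcile the 20% allowance and the 25 + 25 allocation with the replacement rule in Materials and methods: say which losses are replaced, and whether the 20% is meant before or after replacement.

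The cost is a few sentences of text. No extra enrolment is needed. The downside is that the stated attrition tolerance or power will look slightly less favourable.
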